*Daily Experience* We will use mobile-based ecological momentary assessment (EMA) to capture daily experiences. EMA is a brief survey designed to repeatedly assess individuals’ daily events, experience, and contexts multiple times a day to obtain “snapshots” of their everyday lives [46]. The EMA survey will be administered via a smartphone app, mEMA (illumivu). Illumivu is a commercially available EMA platform widely used by behavioral science researchers. EMA surveys will be prompted up to 6 times, at random intervals throughout the day, for 10 days. The random prompt window will be calculated by dividing the waking period (i.e., from participant’s typical wake time to typical bedtime) by 6, and one EMA survey will be prompted/delivered randomly during each time window. All EMA survey items to be used have been carefully selected from relevant previous studies. To capture *perceived racial discrimination and microaggression*, we will use adapted items from the Experiences of Discrimination (EOD) [47] and Gendered Racial Microaggressions Scale (GRMS) [48]. As in previous EMA studies [49], items for *mood/affective states* are chosen based on the two fundamental dimensions of affect suggested by the circumplex model (i.e., positive and negative affect). *Perceived stress* will be assessed using two items from the Perceived Stress Scale [50]. Each EMA survey will take no more than 3–5 min to complete. Responses to the EMA surveys will be automatically uploaded to the illumivu’s cloud-based server, and will be download for data analysis upon data collection completion.

*Salivary Cortisol* Saliva samples will be collected four times a day (i.e., at wakeup, 30 min after waking, before dinner, and right before bedtime) for 3 consecutive days (2 weekdays and 1 weekend days) to capture diurnal patterns of stress across the day. We will follow the collection procedures that have been used in previous studies that demonstrated high feasibility in women [51, 52]. We will use the Salivette device (Sarstedt, Inc.), a small, cotton dental sponge swab. Participants will be asked to place the swab in their mouth for 2 min and to store the samples in their home freezer as soon as possible after each collection. At the end of the 10-day study period, we will retrieve all saliva tubes from each participant and store them at a -80ºC freezer until they are assayed in batches.

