### Statistical considerations

Multilevel linear mixed-effect models will be used to account for repeated measures (for daily behaviors and daily experience) within an individual. We will separate the between-person and within-person effects by partitioning the variance. **Aim 1**: The daily experience predictors include (1) racial discrimination (i.e., daily EOD and GRMS score), (2) mood/affective states (i.e., daily average of positive and negative affect), (3) daily stress (i.e., daily average of perceived stress and diurnal cortisol rhythm such as total cortisol output, cortisol awakening response, diurnal cortisol slope). The daily behavior outcome variables include total daily moderate-to-vigorous physical activity minutes, total sedentary minutes, and sleep variables (i.e., SOL, WASO, TST). We will link the predictor and outcome at the day-level so that the acute impact of daily experience on behaviors can be examined. **Aim 2**: Outcome variables are indicators of cardiovascular health from lab-based measurements. We will first test the direct independent effects of daily behaviors on cardiovascular health outcomes using the mixed-effect models. Next, we will add the single-level and cross-level interaction terms to each multilevel mixed-effect model to test the moderation effects of daily experience. **Aim 3**: We will test the direct independent effects of neighborhood-level characteristics (predictors) on daily behaviors and daily experience (outcome variables) using the mixed-effect models. All tests of the hypotheses will be two-sided and an alpha level of 0.05. All analyses will be performed using SAS 9.4.

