*Sample size and power* Statistical power for evaluation of this study’s objectives was calculated using the macro by Westfall et al. that achieves power estimations based on linear mixed models [56]. Power calculations were computed based on a “fully-crossed” repeated measures design with a two-sided alpha of 0.05. This study will enroll 80 participants. Table 1 displays the statistical power based on possible effect sizes based on adjusted Cohen’s *d* values. Although pilot studies are commonly underpowered, adequate power will be achieved if our study effect is greater than *d* = 0.30. This estimate is indicative of a high likelihood of the planned sample size’s statistical power. We anticipate minimal missing data in the study. However, in the unlikely case of considerable missing data, we will conduct sensitivity analysis to account for different missing data mechanisms (missing at random or missing not at random), using appropriate approaches, such as multiple imputation, pattern-mixture, or selection models [57].

**Table 1 Tab1:** Effect sizes and statistical power yields for *n* = 80

Effect Size		Small			Moderate
Cohen’s *d**	0.10	0.20	0.30	0.40	0.50
Statistical Power (1-*b)*	0.17	0.51	0.84	0.98	0.99

*adjusted for repeated and correlated observations

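### Table 1's power of 0.84 at d = 0.30 comes from a fully-crossed design and is not supported for Aim 1's within-person discrimination effect, to which women with an unvarying score add nothing

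*Protocol article*

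**What the plan says.** All of this stands in the protocol article.

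- **Power basis (Statistical considerations, sample size and power).** "Power calculations were computed based on a “fully-crossed” repeated measures design with a two-sided alpha of 0.05". "This study will enroll 80 participants". The calculation is presented as covering the study's objectives in general.
- **Result (Table 1).** For d = 0.10 to 0.50 the power row reads "0.17 0.51 0.84 0.98 0.99". A footnote says that d is adjusted for repeated and correlated observations, without giving the correlation or variance components. The text concludes that "adequate power will be achieved if our study effect is greater than" d = 0.30.
- **Aim 1 model (Statistical considerations).** "The daily experience predictors include (1) racial discrimination (i.e., daily EOD and GRMS score"), followed by affect and stress. Predictor and behaviour are paired by day, and "We will separate the between-person and within-person effects by partitioning the variance". "All tests of the hypotheses will be two-sided and an alpha level of 0.05".
- **Data collection (Ambulatory assessments).** "EMA surveys will be prompted up to 6 times, at random intervals throughout the day, for 10 days". The study is observational, so discrimination is recorded as it occurs and is not assigned.

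**The concern.** In a fully-crossed repeated measures design every participant is observed under every condition, so all 80 women contribute a full contrast. Aim 1 does not guarantee this for discrimination. The days are each woman's own, and her score on them is whatever she happens to report. Once the within-person part is separated out, her contribution depends on how much her score moves around her own mean over the 10 days. If it does not move, she contributes nothing to that coefficient.

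Discrimination is the first-listed Aim 1 predictor and central to the study's rationale. A reader told that power is adequate above d = 0.30 could take a non-significant result as evidence against an effect of that size, when the study may have had a modest chance of detecting it.

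**Working it through.** **Inputs from the article:** 80 women, 10 days, two-sided alpha 0.05, and Table 1. **Assumed, because not given:** the correlation behind Table 1, the share of women with a varying score, the share of exposed days, and the variance components.

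**1. Reproduce Table 1.** Take a paired layout in which every woman is seen in both conditions:

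ncp = d × √(n / (2(1 − r))), df = n − 1.

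With n = 80 and an assumed r = 0.6, ncp = d × √(80/0.8) = 10d. The noncentral t with 79 df gives 0.17, 0.51, 0.84, 0.98 and 0.999. All five cells agree with the table to within 0.01. The table is consistent with all 80 women contributing.

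**2. Let only a share s of women have a varying score.** Then ncp = 10d√s and df = 80s − 1. At d = 0.30:

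| Share varying | Women | ncp | Power | d for 80% power |
|---|---|---|---|---|
| 100% | 80 | 3.00 | 0.84 | 0.28 |
| 90% | 72 | 2.85 | 0.80 | 0.30 |
| 70% | 56 | 2.51 | 0.69 | 0.34 |
| 50% | 40 | 2.12 | 0.54 | 0.41 |
| 30% | 24 | 1.64 | 0.35 | 0.53 |

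**3. Express this by frequency of exposed days.** This simplifies the score to yes/no per day. Let π be the share of exposed days, independent and equal across women.

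- Share of women with both kinds of day: 1 − (1 − π)^10 − π^10.
- Mean within-woman information relative to a 5/5 split: 9π(1 − π)/2.5.

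The lower power treats all error as day-to-day residual (ncp = 3√(relative information), df 79). The upper treats all error as between-woman slope variation (ncp = 3√(share with both), df = women with both − 1).

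| Exposed days | Women with both | Relative information | Power at d = 0.30 |
|---|---|---|---|
| 5% | 32 | 0.171 | 0.23–0.45 |
| 10% | 52 | 0.324 | 0.39–0.66 |
| 20% | 71 | 0.576 | 0.61–0.80 |

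If reports cluster in some women (beta-binomial, exposure intraclass correlation 0.2), the relative information is multiplied by 0.8. About 19, 34 and 55 women then have both kinds of day, and power is 0.19–0.28, 0.33–0.48 and 0.52–0.68.

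**4. A model favourable to the plan.** Take d in units of the unadjusted total SD, a random intercept only, no slope variance, and outcome intraclass correlation ρ:

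power = Φ(0.30 × √(80 × 9π(1 − π)/(1 − ρ)) − 1.96).

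At π = 10%, 80 × 9 × 0.09 = 64.8. For ρ = 0.2, √(64.8/0.8) = 9, so power = Φ(2.70 − 1.96) = 0.77. For ρ = 0.4 and 0.6 it is 0.88 and 0.97. At π = 5% the three figures are 0.50, 0.62 and 0.79. Power of 0.80 is reached at about 11%, 8% and 5% of days for ρ = 0.2, 0.4 and 0.6. With exposure clustering of 0.4 it is reached at about 20%, 14% and 9%.

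**The case against.** **The predictor is a score, not a yes/no day.** This stands. With up to six prompts a day and microaggressions included, the score may vary in many women. A reader might infer that a woman exposed every day also drops out. She does not if her level changes from day to day; only an unvarying score is uninformative. Step 3 is therefore a simplification, and step 2 is the more direct statement.

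**The frequency is assumed.** This also stands. A reader might infer that the study is underpowered for discrimination as a matter of fact. The article gives no frequency, and step 4 shows that the claim can hold at moderate ones. However, Table 1's footnote says that d is already adjusted for repeated observations, so it is doubtful that step 4's gain from repeated days can be credited again.

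**The scale of d is not stated.** If d were per SD of the predictor, low variation would shrink d itself and not the power at a given d. The loss would then appear in the effect size. That is a reason to state the scale, not a defence of the unqualified sentence.

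**Table 1 is not miscalculated.** Correct. A reader might also infer that it presumes 80 common stimuli that the study lacks. The row cannot show this: the paired layout fits, and so does a crossed layout of 80 women by 10 days. With assumed variance shares of 0.18 (participant-by-condition), 0 (stimulus-by-condition) and 0.4 (residual), ncp = d/(2√(0.18/80 + 0.4/1600)) = 10d.

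**The text is already hedged, and an article leaves detail elsewhere.** It does say that pilot studies are commonly underpowered. But it then states adequacy above d = 0.30 without limiting it to any predictor. The point is about that statement, not about missing detail.

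**Conclusion.** The point holds in a conditional form. One fully-crossed row for n = 80 does not support adequate power above d = 0.30 for the within-person discrimination effect. On Table 1's own scale, 0.80 at d = 0.30 needs a varying score in about 90% of women (72 of 80). Power is 0.54 at half of them and 0.35 at 30%. With 10% of days exposed and no clustering it is 0.39–0.66 on that scale, against 0.77–0.97 in the favourable model.

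These figures rest on an assumed calibration (r = 0.6), an assumed exposure frequency and a yes/no simplification in steps 3 and 4. They show that the claim is unsupported for this predictor, not that it is false. The point does not extend to Aims 2 and 3. Nor does it carry over equally to affect and perceived stress, which are daily averages and probably vary in most women. It should be corrected, with medium confidence in its size.

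**What to change.** 1. For Aim 1, replace the fully-crossed figure with a simulation of the model to be fitted: 10 days nested in 80 women, a person-mean-centred score and a random slope. State the scale of d and the variance components assumed.
2. Report power and the detectable effect for discrimination over a range of shares of women with a varying score and of exposed-day frequencies (for example 5%, 10%, 20% and 30%). Keep this separate from daily affect and perceived stress. The cortisol predictors, sampled on 3 days, are not covered by a 10-day simulation and would need their own row.
3. Restrict the d = 0.30 sentence to the predictors for which it holds.
4. When reporting Aim 1, give the number of women whose discrimination score varied, and the estimate with its confidence interval.

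The cost is a short simulation, a revised Table 1 and one changed sentence, with no added participants or procedures. The downside is that the stated power for discrimination becomes less favourable.

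### Table 1's repeated-measures power (0.84 at d = 0.30) is offered for all objectives, but Aim 2 has one outcome value per woman and about 0.26 power at that effect, and Aim 3 power depends on an unstated ICC

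*Protocol article*

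**What the plan says.** The paragraph on sample size and power (protocol article, Statistical considerations) says that power for the study's "objectives was calculated using the macro" for linear mixed models. It continues: "Power calculations were computed based on a “fully-crossed” repeated measures design", two-sided alpha 0.05. On size it says: "This study will enroll 80 participants". Table 1, headed "Effect sizes and statistical power yields for" n = 80, lists power of 0.17, 0.51, 0.84, 0.98 and 0.99 at d = 0.10, 0.20, 0.30, 0.40 and 0.50. A footnote says that d is adjusted for repeated and correlated observations. The text then states: "Although pilot studies are commonly underpowered, adequate power will be achieved if our study effect is greater than" d = 0.30. No aim is excepted, and no other power figure is given.

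The three aims have different data structures:

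- **Aim 1** links predictor and outcome day by day within each woman.
- **Aim 2**: "Outcome variables are indicators of cardiovascular health from lab-based measurements". Study procedures places these measurements at the first visit, before the 10-day monitoring begins. Daily behaviours are the predictors, and daily experience is added as a moderator.
- **Aim 3** uses neighbourhood characteristics taken from the home address (Other measures) as predictors, and daily behaviours and daily experience as outcomes.

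**The concern.** Repeated days raise power for an effect that varies from day to day within a woman. They do not multiply an outcome that was measured once. In Aim 2 each woman contributes one value of, say, flow-mediated dilation or CRP, however many days of behaviour are recorded. In Aim 3 the predictor takes one value per woman, so its effect is estimated between women. The repeats only make each woman's mean outcome more precise. A single repeated-measures table therefore cannot serve all three aims.

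Aim 2 carries the vascular hypotheses, and the Discussion intends the results to guide lifestyle interventions. If a reader sets a null vascular result against a claimed power of 0.84, it looks informative. At a true power near one in four it is not.

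**Working it through.** **Inputs.** From the article: n = 80; two-sided alpha 0.05; up to 10 days per woman; Aim 2 outcomes taken once; Aim 3 predictors fixed by address. Assumed here, because the article does not give them: an even split for converting d, and the ICC of the daily outcomes.

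**1. The plan's own figure.** Table 1 cannot be rebuilt from the stated inputs, because the number of crossed repeats and the variance components are not given. One assumed set comes close. Take ncp = d / (2·√(E/(2pq) + PC/p + SC/q)), where p is the number of participants, q the number of crossed repeats, E the residual variance, and PC and SC the participant and repeat-unit variances of the effect. With E = 0.3, PC = SC = 0.1, p = 80 and q = 80, power is 0.167 / 0.507 / 0.843 / 0.977 / 0.999. The table is thus attainable for some crossed design with 80 participants. With q = 10 the same components give 0.25 at d = 0.30.

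**2. Aim 2 main effects.** With two groups of 40, ncp = d·√(40·40/80) = d·√20, on 78 df. At d = 0.30, ncp = 0.30 × 4.472 = 1.342 and power is 0.263. A regression on a continuous predictor with r = d/√(d² + 4) gives the same values.

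| d | r | Table 1 | Between women, n = 80 |
|---|---|---|---|
| 0.10 | 0.05 | 0.17 | 0.07 |
| 0.20 | 0.10 | 0.51 | 0.14 |
| 0.30 | 0.15 | 0.84 | 0.26 |
| 0.40 | 0.20 | 0.98 | 0.42 |
| 0.50 | 0.24 | 0.99 | 0.60 |

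80% power is reached at d of about 0.63, or |r| of about 0.30. At d = 0.30, a power of 0.80 would need about 351 women and 0.84 about 390.

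**3. Sensitivity to the scale of d.** If 0.30 is read as a correlation, ncp = √80 × 0.30/√(1 − 0.09) = 2.81 and power is 0.79 (0.78 by Fisher's z).

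**4. Aim 2 moderation at person level.** For one interaction term on 1 and 76 df, with λ = 80·f², f² = 0.02 gives λ = 1.6 and power 0.24. Power of 0.80 needs f² of about 0.10.

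**5. Aim 3.** If d is in SDs of the woman's mean, step 2 applies and power at d = 0.30 is 0.26. If d is in single-day SDs, the 10-day mean has variance v = ICC + (1 − ICC)/10, and ncp = 0.30·√(20/v).

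| Assumed ICC | v | ncp | Power at d = 0.30 |
|---|---|---|---|
| 0.7 | 0.73 | 1.57 | 0.34 |
| 0.5 | 0.55 | 1.81 | 0.43 |
| 0.3 | 0.37 | 2.21 | 0.59 |
| 0.2 | 0.28 | 2.54 | 0.71 |
| 0.1 | 0.19 | 3.08 | 0.86 |

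The table's 0.84 is reached only near an ICC of 0.1. These values assume 80 distinct neighbourhoods and ten complete days. Shared zip codes or tracts would lower them.

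**The case against.** The best defence has four parts.

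- *The scale of d is undefined.* Table 1's d is adjusted for repeated observations, so a between-woman d of 0.30 need not be the same effect. This is fair, and 0.26 is conditional on the even-split reading. But the more generous reading as a correlation still falls short of 0.84, and no adjustment creates a second lab value per woman.
- *Repeats do help Aim 3.* This stands. It would be wrong to quote 0.26 for Aim 3 as a point value; it applies on the person-mean scale, and power is higher on the single-day scale.
- *It is a minimal-risk pilot and Aim 3 is exploratory.* The article does say that pilots are commonly underpowered, but the same sentence then asserts adequacy. That assertion is what needs correcting.
- *Mixed models are planned throughout.* A mixed model cannot add outcome replication that was not collected.

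Two stronger readings are tempting and not supported. A reader might notice that the first four entries of Table 1 coincide with a paired t-test on 100 units and infer that the table was computed for the wrong n. The macro inputs are not given, and step 1 shows that 80 participants with other inputs fit as well, so no slip is shown. A reader might also discount the power for attrition. The article expects minimal missing data and plans sensitivity analyses, and it gives no loss rate from which to calculate.

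**Conclusion.** The power statement is wrong as written for Aim 2 and unsupported for Aim 3. For Aim 2 main effects, power at d = 0.30 is about 0.26 on an even-split between-woman reading and about 0.79 if 0.30 is a correlation; neither reaches the stated 0.84. On the first reading, the effect detectable with 80% power is about twice the claimed threshold (0.63 against 0.30). Person-level moderation is weaker still for a small effect (0.24 at f² = 0.02). For Aim 3 the claim holds only if the effect is in single-day SDs and the ICC is about 0.1 or lower; the article gives no ICC. Whether Table 1 is right for Aim 1 cannot be settled from the article, and no error is alleged there. The sample size itself is not at issue, only what is claimed for it.

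**What to change.** Limit Table 1 and the d = 0.30 statement to the within-person tests of Aim 1, and state the effect scale, the number of repeats and the variance components used. Then add separate entries:

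- **Aim 2 main effects:** n = 80, 80% power for |r| of about 0.30.
- **Aim 2 moderation:** its own figure, for example f² of about 0.10 for 80% power on a person-level term.
- **Aim 3:** power or detectable effect with the assumed ICC, the scale of the effect, and the number of women or distinct neighbourhoods.

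State that Aims 2 and 3 will be interpreted through confidence intervals, and that a non-significant result there is not evidence of no association. The cost is a revised paragraph and table. No extra participants or procedures are needed, but the stated power becomes less favourable.

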## Discussion

Our long-term research goal is to develop multilevel (i.e., addressing factors at the individual, interpersonal, and social-environmental levels) behaviorally grounded lifestyle interventions to reduce CVD risk, improve the overall health of Black women, and minimize the gaps in racial/ethnic and gender disparities in CVD. To achieve this goal, we will first examine if and how Black women’s daily health behaviors and experiences are influenced by their social and neighborhood environments, and their impact on physiological indicators of cardiovascular health. This study is guided by the SDOH framework, which addresses racial/ethnic disparities in CVD [18]. This study uniquely encompasses determinants of cardiovascular health from multiple levels with a focus on a population that is disproportionately affected by CVD outcomes.

We expect results from our study will offer critical new insights into the risk and protective behavioral factors of cardiovascular health in Black women. We will disseminate the study results to the scientific community (e.g., via scientific conference presentations and peer-review publications) as well as community members who might be interested in this topic (e.g., via our ongoing collaboration with the Tarrant County Health Equity Alliance). Scientific manuscript authorship eligibility will follow the International Committee of Medical Journal Editors’ recommendations [58]. There is a growing recognition that racial/ethnic group data disaggregation is necessary to ensure health equity in racially/ethnically minoritized populations [59]. In other words, identifying behavioral patterns (and factors influencing these behavioral patterns) and environmental context that may explain the within-group differences in cardiovascular health among Black women can provide crucial knowledge to ensure the development of more tailored and effective lifestyle interventions for this population.

## Data Availability

Data sharing is not applicable to this article as no datasets were generated or analysed during the current study.

## Abbreviations

BLOOM: Black women’s Life experience On cardiovascular health via Ongoing Monitoring
CVD: Cardiovascular disease
SDOH: Social determinants of health
CRP: C-reactive protein
IL-6: Interleukin-6
UTA: University of Texas at Arlington
SPIROS: Standard Protocol Items for Observational Studies
IRB: Institutional Review Board
MCA: Middle cerebral artery
ICA: Internal carotid artery
SOL: Sleep onset latency
WASO: Time spent awake after sleep onset
TST: Total sleep time
EMA: Ecological momentary assessment
EOD: Experiences of Discrimination
GRMS: Gendered Racial Microaggressions Scale
